### Plans to give access to the full protocol, participant level-data and statistical code {31c}

Every main investigator will receive a full protocol copy and could also visualize it in REDCap program. In case that a patient would like to consult it, the surgeon will be the one in charge to provide such information. Data will not be publicly available; only the main investigator of each hospital, statistician, and data monitoring committee could visualize it.

The use of data and statistical code is subject to the main investigator decision after signing a written agreement.

## Oversight and monitoring

### Composition of the coordinating center and trial steering committee {5d}

The main research or project team of the trial is created and formed by three surgeons who work in the coordinating center. The project team has the responsibility to control the hospitals included in the trial (provide information, evolution of the inclusion of patients, evolution of CEIM acceptance, and resolve any doubts), control all the patients included in the main investigator hospital, modify the protocol if required and present the modification/s to the ethic committee, and revise the veracity of the data included in the REDCap program.

The trial steering committee is responsible for monitoring and supervise the progress of the study towards its interim and overall objectives. Contact with the main research team must be easy and affordable. The trial steering committee is formed by the main investigator of the trial, the chief of the research unit, a statistician, and the sponsor Cardiolink Group S.L.

The main investigator of each hospital included in the trial is responsible for the patients included in his organization, for verifying the presence of a right informed consent, and for ensuring a correct recruitment of patients and veracity of the data.

The main investigator of the coordinating center will double check all the information and documents provided by the rest of the centers.

### Composition of the data monitoring committee, its role and reporting structure {21a}

An independent data monitoring committee (iDMC) has been created with independent members (clinical, statistical, and methodological expertise). The iDMC is independent from the sponsors and depends from the coordinating center.

### Adverse event reporting and harms {22}

Throughout the study, every effort should be made to detect and evaluate adverse events or harmful findings. If adverse events occur, the primary concern is for the safety and well-being of the subject. Appropriate medical intervention will be undertaken. This includes all adverse events or complications observed by the investigator or reported by the subject, whether or not caused by the surgery under study. The relationship of the adverse event to the surgery will be assessed by the investigator and documented in the case report form (CRF). The investigator should complete the entire CRF and notify the sponsor for review, including a description of the event, the date of onset, an assessment of its relationship to the surgery, a medical assessment of its severity, the actions taken, whether the study surgery had to be discontinued, and the resolution of the event. Serious adverse events that continue to exist at the end of the study period should be followed up to determine the final outcome. Any adverse event that occurs after the study period and is considered possibly related to the study surgery or study participation should be recorded and reported immediately. A pre-existing condition, i.e., one that was present at the start of the study, should be recorded as an adverse event if its frequency, intensity, or nature worsens during the study period.

The sponsor is responsible for adverse event classification and ongoing safety assessment of the clinical investigation and shall:Review the investigator’s assessment of all adverse events and document in writing their severity and relationship to the experimental intervention. In case of disagreement between the sponsor and the principal investigator, the sponsor shall communicate both opinions to the Investigation Ethics Committee (IEC) and to the national competent authorities, if necessaryReport or ensure that the principal investigator reports, all serious adverse events to the IEC. The investigator should report any serious adverse events to the sponsor and the local IRB as soon as he/she becomes aware of them, by fax/telephoneReport all serious adverse events to the competent authorities within the required time period, if required by national lawsInform all local principal investigators, in writing, of all serious adverse events reported to the sponsor and ensure that they report them to their IECs if required by national law. This information should be sent to all principal investigators within a time period established on the basis of potential riskEnsure that any new information on the clinical investigation is communicated to the competent authorities

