**Methods:**

This is a prospective, multicenter, international, and randomized clinical trial. Patients undergoing conservative surgery and axillary lymphadenectomy for breast cancer will be randomized to control group (lymphadenectomy without sealant) or interventional group (lymphadenectomy with sealant Glubran 2®). In any of the study groups, drains are placed. Patients who received neoadjuvant treatment are included. Measurements of the study outcomes will take place at baseline; at 7, 14, and 30 days post-surgery; and at 6–12 months. The primary outcome is symptomatic seroma. Secondary outcomes are seroma volume, morbidity, quality of life, and lymphedema.

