### Main safety measures

The main safety measures are as follows: adverse events and post-surgical complications such as suture failure and surgical wound infection.

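### Investigator and sponsor rate adverse-event causality against different things: the surgery, which both arms undergo, and the experimental intervention, which only one arm receives

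*Protocol article*

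**What the plan says.** All the procedural text is in the protocol article, section Adverse event reporting and harms {22}.

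- **Investigator's rating.** "The relationship of the adverse event to the surgery will be assessed by the investigator and documented in the case report form (CRF"). The report that goes to the sponsor repeats that reference: "an assessment of its relationship to the surgery, a medical assessment of its severity, the actions taken, whether the study surgery had to be discontinued". This part of the section does not mention the sealant.
- **Sponsor's rating.** The first of the sponsor's duties is: "Review the investigator’s assessment of all adverse events and document in writing their severity and relationship to the experimental intervention".
- **Disagreement rule.** "In case of disagreement between the sponsor and the principal investigator, the sponsor shall communicate both opinions to the Investigation Ethics Committee (IEC"). Where necessary, national authorities receive them too.
- **Scope of collection.** "This includes all adverse events or complications observed by the investigator or reported by the subject, whether or not caused by the surgery under study".

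Three other places set the context. In the abstract, under Methods, patients are "randomized to control group (lymphadenectomy without sealant) or interventional group (lymphadenectomy with sealant Glubran 2". Under Main objectives, the safety and tolerability of Glubran 2 is one of two main objectives. Under Main safety measures, the measures are "adverse events and post-surgical complications such as suture failure and surgical wound infection", with no restriction to related events.

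**The concern.** A causality rating helps only if it refers to the thing under test. Here that is the sealant, because lymphadenectomy is done in both arms. A rating against the surgery cannot separate a reaction to Glubran 2 from ordinary morbidity of the dissection.

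The sponsor is asked a different question about the same event, yet the two answers are to be treated as opinions that can agree or disagree. Two things are at stake:

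- whether the escalation rule on causality does what it is meant to do;
- whether the surgeon, who applied the product and follows the patient, is ever asked about the product.

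**Working it through.** The document states no figure on this point, so the main check sets the two rules side by side.

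| | Investigator | Sponsor |
|---|---|---|
| Severity | medical assessment of severity | severity, after reviewing the investigator's assessment |
| Causality reference | the surgery | the experimental intervention |
| Present in the control arm? | yes | no |

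On severity the two parties answer the same question, so the disagreement rule works. On causality they do not. Take a wound infection in a sealant patient and compare the recorded answers with the parties' real views:

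1. **Both think the dissection caused it.** The investigator records related (to surgery) and the sponsor records unrelated (to the intervention). The records differ although the views do not: a false disagreement.
2. **The investigator suspects the glue, the sponsor the dissection.** The investigator can only express the suspicion as related to surgery, and the sponsor records unrelated. The pair of records is the same as in case 1, so a real disagreement looks like a false one.
3. **The investigator suspects the dissection, the sponsor the glue.** Both record related. The records match and a real disagreement is hidden.

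Cases 1 and 2 cannot be told apart from the ratings, and case 3 triggers nothing.

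**How often this could arise.** The background section gives wound infection after lymphadenectomy as 5–15%. Assuming that range holds in this trial, 67 patients per arm give 0.05 × 67 = 3.4 to 0.15 × 67 = 10.1, or roughly 3 to 10 infections per arm. For each of these in the sealant arm, relatedness to surgery would be a natural answer whatever the role of the glue. This is an illustration, not a forecast.

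**Why case-level attribution still has a use beside the comparison by arm.** Suppose a reaction occurs only in the sealant arm and never in controls. With 67 per arm, Fisher's two-sided p for k events against 0 is 2 × C(67,k)/C(134,k):

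- k = 5: 2 × (67·66·65·64·63)/(134·133·132·131·130) = 0.058
- k = 6: the value for k = 5 multiplied by 62/129 = 0.028

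So six cases, 6/67 = 9.0% of the sealant arm, are needed before the planned test reaches p < 0.05. If the 10% loss came out of the 67, leaving about 60 per arm, six cases are still needed (p = 0.057 for five, 0.027 for six). For rarer product reactions, the judgement on each case is the main source of information.

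**The case against.** The strongest case on the other side is that little depends on this rating.

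- **The main safety comparison does not use it.** Events are collected whatever their cause, the safety measures have no relatedness filter, and the statistical section applies the same tests to them. Because the surgery is common to both randomised arms, that comparison is what isolates the sealant. This stands. A reader might infer that the main safety objective cannot be met; the document does not support that.
- **Serious events are reported regardless.** The sponsor's duties cover all serious adverse events, with no condition on relatedness. This stands.
- **Late events are covered more broadly.** For events after the study period, the trigger also includes a possible relation to taking part in the study, which can take in the sealant. This stands, and that sentence needs no correction.
- **The disagreement rule is not void.** It works for severity. A reader might call the rule inoperable, but the defect is confined to causality.
- **The surgery under study may mean the allocated operation, sealant included.** This reading is possible, though the text does not give it. It would make the wording loose rather than contradictory, but one combined rating would still not separate glue from dissection, and the sponsor's reference would still differ.
- **The case report form is not shown.** It may hold a separate sealant item, so nothing can be asserted about its fields. The mismatch, however, lies in the stated procedure and is not a detail left to a fuller document.
- **Sponsor influence.** A reader might infer that product attribution rests with the sponsor unchecked. The article describes an independent data monitoring committee that meets every six months. It gives that committee no stated role in causality, so the point supports neither side.

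**Conclusion.** The point holds as a mismatch in the stated procedure, and the text should be corrected. On causality, the investigator and sponsor are asked different questions about the same event, so the escalation rule can misfire in both directions. The procedure as described also yields no investigator judgement on relatedness to Glubran 2.

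The size is modest. It touches the causality assessment of each adverse event in the sealant arm and changes no endpoint, test or sample size. It matters mainly for product reactions too rare to show in a comparison of 67 against 67, which by the calculation above means those seen in fewer than about 9% of sealant patients when controls have none.

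The conclusion rests on two readings: that the surgery means the operation common to both arms, and that the experimental intervention means the sealant. The abstract's description of the arms supports both.

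**What to change.** In the section on adverse event reporting and harms {22}, use the same causality reference for both parties:

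1. The investigator rates each event's relationship to the axillary surgery, in both arms.
2. In the sealant arm, the investigator also rates relationship to Glubran 2, as a separate item.
3. The sponsor reviews those same items, and the disagreement rule applies item by item.
4. The case report form is checked against this wording and aligned if it differs.

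Keep the comparison of all adverse events by arm, whatever their cause, as the main safety result. The section on implementation {16c} says the surgeon knows the allocation, so a sealant-relatedness rating is unblinded and exists in one arm only. It should support case review and reporting, not serve as a between-arm outcome.

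The cost is one extra item per event in the sealant arm, matching wording in the two parts of the section, and acceptance that the added rating is open to bias. Design, sample size and patient care do not change.

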### Frequency and plans for auditing trial conduct {23}

The project team met every week at the beginning of the project. After the elaboration of the trial and the start of the inclusion of the first patients, meetings will take place every month or more often (ad hoc) if required.

The trial steering committee will initially meet monthly. The coordinating center and the trial steering committee will periodically check the evolution of the research, revising the data included by each center, and contact to them if needed. The main investigator will update the trial steering committee with any new information on the trial at an annual meeting (or ad hoc if requested).

The trial will be monitored and audited by the main investigators and sponsor.

The independent data monitoring committee will meet every 6 months or more often if required.

The ethics committee will evaluate the protocol only if modified by the main investigator and presented for evaluation. Any modification of the protocol must be approved by the ethics committee.

### Plans for communicating important protocol amendments to relevant parties (e.g., trial participants, ethical committees) {25}

In case of trial modification, it will need to be approved by the IEC of the coordinating center and modify in ClinicalTrials.gov. Main investigator of the coordinating center will inform about the changes to the rest of the hospitals involved. All changes will be modified in the protocol, adapting the version and date.

### Dissemination plans {31a}

The principal investigator declares his commitment to publish the final results of the study in a scientific publication, and the results will be showed in scientific conferences.

The ICMJE’s recommendations regarding authorship according to the following four criteria shall be taken into account:Substantial contribution to the conception or design of the work or to the acquisition, analysis, or interpretation of data for the workDrafting of the paper or critical revision of its important intellectual contentFinal approval of the version to be publishedCommitment to be responsible for all aspects of the work by ensuring that all questions concerning the accuracy or honesty of any part of the work have been properly investigated and resolved

All persons qualifying as authors according to the ICMJE will be asked to sign an authorship contract.

The inclusion of a minimum of 5 patients per center is required. In case of including 10 patients, the name of the collaborating author in that center will appear in the title of the future scientific publication (as long as they meet the criteria of ICMJE’s recommendation). The order of authors in the scientific publication will depend on the inclusion contribution of each one. If there happens to exist a limit on the number of authors in the scientific journal, the inclusion of the remaining authors will be assessed as “Breast Cancer Research Group.”

## Discussion

The project aims to investigate an alternative therapeutic strategy in BC patients undergoing AL, a highly prevalent disease around the world with a high care burden in our health system.

Assuming that seroma will always appear, inherent to the surgical procedure, we directed aims not to prevent its formation but to prevent its symptoms. With this aim in mind, we decided to investigate over the use of Glubran 2® in axillary surgery. Scientific literature reports good results when using Glubran 2® as a hemostatic agent (liver, kidney, spleen, pancreas) [13], as a sealant (blood vessels, lymphatic vessels, anastomosis), an adhesive (abdominal or inguinal meshs), as a shutter of fistula tracts [11], and in many other surgical procedures. So, we chose this product for its sealant, adhesive, and hemostatic properties, thinking that it would help us reduce the death space but also would control of lymphorrhea and seroma formation in the axillary cavity.

Our main objective is to determine if the use of this sealing product has any role in diminishing the seroma formation; another is to find out if Glubran 2® is capable of reducing the pain and other symptoms related to AL. All patients will keep a close follow-up, and periodical QoL test will be held, in order to detect any major discomfort as quickly as possible.

Performing an AL is a common and regulated procedure in all breast cancer centers; therefore, there should not be a difference in this practice between hospitals. Moreover, being this study multicenter and international improve its external validity.

Where there is a difference between hospitals, regions, and countries is in relation to the postoperative regime. In our hospital, patients undergoing an AL (who are ASA < 4 and absence of adequate cognitive capacity or family support) no longer stay in the hospital. Since 2021, we perform a protocol of outpatient surgery with the collaboration of “Day Hospital Unit,” so that patients can sleep at their homes the day of the surgery, the following day receive a visit of a doctor and a nurse at home to asses’ pain control and seroma formation, and in a week come to the hospital for a clinical assessment by the surgeon. However, they can phone contact with the breast cancer nurse anytime in case of doubt. However, many of the participating hospitals perform AL in an impatient regime. Being this item non-relevant for the objectives of the study and having no impact in its results, we did neither collect nor analyze this data.

We intend to assess whether patients subject to AL without placement of drains have a correct QoL, with the aim of changing a paradigm, justifying and generalizing the non-benefit of using an axillary drain. The results of the present trial will be highly relevant and will allow a large number of patients undergoing an AL to benefit from a less morbid, less painful, but equally effective seroma management.

Although the current tendency in the treatment of BC is to reduce the number of AL practiced to our patients, caring about reducing the discomfort associated with the procedure and reducing the rate of clinical axillary seroma will for sure be appreciated by our patients.

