The usual clinical practice in these procedures includes the placement of an axillary aspirative drain, which is usually removed when the amount of drainage collected is low enough. However, this clinical practice is questioned by some authors [5]. Given its high incidence, several groups have made efforts to achieve a reduction and better control of seroma [3], noting that most of them use suction drains after surgery. According to the conclusions published by Cochrane in 2013, there is limited evidence that the insertion of a drain after axillary lymphadenectomy reduces the likelihood of developing seroma and/or reduces the number of aspirations needed to control it [5]. Given the current evidence regarding the use of drains after lymphadenectomy, in our study, we decided not to use drains after regular axillary lymphadenectomy.

Efforts to control and reduce the seroma volume after AL and therefore help our patients improve their recovery and have a better QoL have been made but without any significant results that lead us to change clinical practice yet. Some teams suggest the use of sealants and/or biological glues [6]; however, to date, there are still no relevant results to allow clinical practice to change [7]. Studies assessing the use of such sealants include patients with and without drains. Currently in breast cancer, percentages close to 20–25% of symptomatic seroma requiring drains are described [8, 9].

There is a large amount of conflicting scientific evidence regarding current management of seroma after AL. However, there is a lack of evidence stablishing a relationship between the volume of the axillary seroma and its symptoms. Moreover, the effect of tissue sealants in seroma control without using suction drains has not been sufficiently investigated either. For this reason, the present study is a randomized multicenter international clinical trial that aims to analyze the role of a tissue sealant in seroma production and in the control of pain-related-to-seroma in patients with BC undergoing LA without a drain placement.

Glubran 2® is a synthetic surgical glue with a cyanoacrylic base modified by the addition of a monomer synthesized by the manufacturer, approved for its use in surgery for its hemostatic, sealing, and adhesive properties that facilitate strong tissue adhesion. Its active ingredient is N-butyl-2-cyanoacrylate + methacrylosulpholane.

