### Trial design {8}

This is a multicenter, international, prospective, double-arm randomized clinical trial with a superiority design. Baseline data will be measured prior to randomization. Follow-up data will be collected at 7, 14, and 30 days after randomization. Long follow-up data will be collected at 6 and 12 months. A CONSORT diagram is presented in Fig. 1.

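### The Discussion aims to show that an axillary drain brings no benefit, but drain use does not differ between the arms, so the trial can answer only the sealant question

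*Protocol article*

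**What the plan says.** Four parts of the protocol article bear on this point.

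- **Randomised contrast.** The abstract's Methods say that patients "will be randomized to control group (lymphadenectomy without sealant) or interventional group (lymphadenectomy with sealant Glubran 2"®). Trial design {8} calls the study a "double-arm randomized clinical trial with a superiority design".
- **Drain use.** Background and rationale {6a} records a study-wide choice: "in our study, we decided not to use drains after regular axillary lymphadenectomy". It places the research question "in patients with BC undergoing LA without a drain placement". The main objectives, both efficacy and safety, are likewise framed as lymphadenectomy without a drain.
- **Claim about drains.** The Discussion plans to assess quality of life in undrained patients with the aim of "justifying and generalizing the non-benefit of using an axillary drain". It then says that the results will let many patients benefit from "less morbid, less painful, but equally effective seroma management".
- **A conflicting sentence.** The abstract's Methods also state: "In any of the study groups, drains are placed".

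**The concern.** To say that a drain brings no benefit is to make a comparative statement about drained and undrained patients. The trial as described has no contrast between them. The Background calls a drain the usual practice and describes the evidence on its effect as limited, so the article itself treats the drain question as open.

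The risk lies in what is concluded once results are in. If the sealant works, the trial has shown that sealant beats no sealant among undrained patients. If it does not work, or if quality of life is good in both arms, nothing follows about how the same patients would have fared with a drain. A reader who took the Discussion at its word could present either result as randomised evidence for abandoning drains.

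**Working it through.** **1. The plan's own figure and what it powers.** Inputs from Sample size {14}: 25% symptomatic seroma in controls, 7% with sealant, two-sided alpha 0.05, beta 0.2, loss to follow-up 10%, and 67 per arm.

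Arcsine formula: n = 2 × [(z for alpha + z for power) / h]², where h = 2·arcsin√0.25 − 2·arcsin√0.07.

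- h = 1.0472 − 0.5355 = 0.5117
- z sum = 1.960 + 0.842 = 2.802
- n = 2 × (2.802 / 0.5117)² = 59.96 per arm, so 60
- allowing for loss: 59.96 / 0.90 = 66.6, so 67

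The stated 67 per arm is reproduced. Both rates in this calculation belong to the sealant contrast, and no drained rate enters it.

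**2. Information on a drain effect.** A drain effect would be the seroma percentage with a drain minus the percentage without. Its variance is p₁(1−p₁)/n₁ + p₀(1−p₀)/n₀, where n₁ is the number of drained patients. With no drains used, n₁ = 0 and the first term is undefined. No estimate, interval or power exists.

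- If 67 already includes the loss, the total is 2 × 67 = 134, with 0 drained.
- If the loss is added on top, 67 / 0.90 = 74.4, so 75 per arm and 150 in total, still with 0 drained.

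**3. The abstract's sentence taken literally.** If drains were placed in both arms, n₀ would be 0 instead of n₁. Drain use would still not vary between arms, so the result is the same under either reading.

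**4. Could another part of the protocol supply the comparison?**

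| Section | Content on drains |
|---|---|
| Objectives {7} and main hypothesis | Effect and safety of the sealant, and secondary aims between the study groups; no drain effect |
| Outcomes {12} | Puncture-aspiration, pain, volume, visits, readmission, lymphoedema, quality of life; none compared with drained patients |
| Trial design {8} | Superiority, two arms |
| Sample size {14} | Sealant versus no sealant only |
| Statistical methods {20a}, additional analyses {20b} | No drained or historical comparator, no equivalence or non-inferiority margin |

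Nothing in the article supplies a drained reference.

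**5. Scope of generalising.** Eligibility criteria {10} exclude patients who need a mastectomy, although the Background says seroma is mainly seen after mastectomy and lymphadenectomy. Even a descriptive statement about undrained patients therefore applies to conservative surgery only.

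**The case against.** The strongest reply is that this is Discussion prose and not part of the plan. No objective, hypothesis, endpoint or analysis proposes a drain effect. The same Discussion gives the main objective as the role of the sealing product, and the abstract's own discussion hopes only that patients may benefit from a sealant without drains. This stands as to weight. A reader might infer that the non-benefit of drains is a planned headline result or a formal objective, and the document does not support that. It does not remove the point, because the sentence is worded as an aim and concerns changing usual practice.

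A second reply concerns "less morbid, less painful, but equally effective seroma management". A reader might take this as a claim of equivalence to drained care, and so fault the superiority design for lacking a margin. The phrase names no comparator. The preceding sentence makes drains a plausible reading, but sealant without a drain fits too. The criticism is therefore conditional: if drained care is meant, a superiority design with no drained arm cannot show it.

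A third temptation is to set the control arm's seroma percentage against the literature figures in the article. This would support neither side. The 19% in the abstract is explicitly for lymphadenectomy without drains, and the 20–25% in the Background follows a sentence on studies with and without drains. Neither is a drained benchmark.

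Finally, describing undrained outcomes is legitimate, and the Background rests the decision that "we decided not to use drains after regular axillary lymphadenectomy" on an outside review and not on this trial. That stands: the description is useful, provided no inference about drains is drawn from it.

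**Conclusion.** The point holds as one of interpretation. The stated aim on drains cannot be met by this design. The gap is structural: no patient contributes to a comparison of drain with no drain, whatever the sample size and whichever reading of the abstract is taken. The trial can estimate the effect of sealant versus no sealant in patients managed without a drain.

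The no-drain design agrees with the formal objectives, and the randomisation, primary endpoint, sample size and primary analysis are untouched. The correction matters because it changes what the trial may conclude.

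This rests on two assumptions: that the two arms described are the only ones, and that no drained comparison group is used elsewhere. The article mentions none.

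The abstract's sentence on drains is a separate conflict with the Background and the Objectives. It probably reflects a slip in wording, and it adds no weight to the main point.

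**What to change.** - Delete the Discussion's statement on the non-benefit of a drain, or narrow it to describing outcomes in patients managed without one.
- Delete the phrase on equal effectiveness, or name its comparator. If the comparator is drained care, the phrase cannot stay under the present design.
- State that conclusions are limited to sealant versus no sealant in patients managed without drains.
- State that outcomes in undrained patients, including quality of life and the control-arm percentage of symptomatic seroma with its confidence interval, are descriptive only, with no inference about drains.
- Separately, reconcile the abstract's sentence on drain placement with Background and rationale {6a} and Objectives {7}, so that all three describe the same management.

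The cost is a few sentences of text. No data collection, sample size or analysis changes. The downside is that the stated ambition becomes narrower.
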